#### Sex and Gender Considerations

In light of research finding that the intended pregnant individual experiences the most distress in the context of infertility, we will only recruit individuals who have a uterus. However, we will ensure that this study is welcoming to individuals of all gender identities and sexual orientations, as this study will aim to contribute to current knowledge surrounding the psychological experiences of individuals from minority genders, and sexual groups experiencing infertility. This study materials including advertisements, will use inclusive language. Advertisements will not use the word “woman” but instead “individuals attempting to get pregnant but experiencing infertility.” The intervention itself has also been designed with inclusive language, a gender-neutral design, and pictures of individuals from diverse backgrounds and sexual orientations. To ensure adequate diversity among our participants, we will advertise on subreddits specifically targeting members of the LGBTQIA+ (lesbian, gay, bisexual, transgender, queer, intersex, and asexual) community.

#### Participant Screening and Enrollment

Prospective participants will be emailed the link to a web-based eligibility survey. If found to be eligible, they will be asked to provide their contact information, and a research assistant will contact them to schedule an enrollment session through videoconference.

During the Zoom-facilitated remote enrollment session, eligibility will be confirmed, a brief introductory video explaining the study and intervention will be presented, and consent will be obtained. An enrollment session in which visual contact is made will ensure that our recruited participants are not simply “bots” posing as eligible participants. During the session, participants will complete the baseline questionnaires through a link emailed to them by the research assistant. Upon completion of the questionnaires, the research assistant will open an opaque envelope, revealing the participant’s random assignment to either the treatment or control condition. The research assistant will then ask the participant which day of the week they would like to receive their weekly module video (if assigned to the treatment condition) or weekly outcomes survey (if assigned to the control condition).

#### Participant Safety

Participants endorsing suicidal ideation on question 9 of the PHQ-9 at baseline will be permitted to participate in the study but will be informed that their level of risk will be reassessed weekly. Specifically, each week, they will receive a survey question, “Please pick out the one statement that best described how you have been feeling during the past week, including today: (A) I don’t have any thoughts of killing myself. (B) I have thoughts of killing myself, but I would not carry them out. (C) I would like to kill myself, or (D) I would kill myself if I had the chance.” If participants choose either C or D, a message including contact information for 2 suicide hotlines will appear. As well, an automatic notification will be sent to the study therapist, flagging the response. They will then follow up with the participant immediately by phone, at most within 24 hours. If participants endorse A or B, they will simply be allowed to continue with the program.

In addition, the presence of active suicidal ideation (presence of a plan or intent) will be assessed by the researcher during the Zoom-facilitated enrollment session. Those endorsing active suicidal ideation will be referred to additional in-person mental health resources available in their geographic area. They will be given access to the program for their own benefit but will not be enrolled in the study.

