### Participants

#### Inclusion and Exclusion Criteria

Based on our sample size calculations, we will recruit 170 women, recruited through the web. The inclusion criteria will include the following: is infertile as defined as either actively attempting to conceive for ≥12 months without success or is currently undergoing fertility treatments (eg, ovulation induction medication, IVF, and intrauterine insemination). This definition ensures that this study is inclusive of both individuals who cannot afford fertility treatments and women who are in same-sex couples and cannot conceive naturally. Though the original funded protocol excluded individuals reporting active suicidal ideation, those already receiving psychotherapy, and those with high levels of fertility-related quality of life (FertiQoL above 70), we have since decided to remove these exclusion criteria in order to closely estimate the program’s anticipated real-world effectiveness. Rather than exclude individuals based on baseline quality of life, we will perform secondary analyses, considering baseline quality of life as a treatment moderator.

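### The weekly suicide-risk question never asks about a plan, so a flagged participant who forms a plan after entry but disclaims acting can answer B and trigger no safety step

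*Protocol article*

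**What the plan says.** The Participant Safety section describes two checks.

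- **At entry.** The section states that "the presence of active suicidal ideation (presence of a plan or intent) will be assessed by the researcher during the Zoom-facilitated enrollment session". What follows is a referral and non-enrollment: "Those endorsing active suicidal ideation will be referred to additional in-person mental health resources available in their geographic area", and "They will be given access to the program for their own benefit but will not be enrolled in the study".
- **After entry.** Participants who endorsed PHQ-9 item 9 at baseline may take part and are told that their risk will be reassessed every week. They pick one of four statements. A denies any thoughts; the next option reads "B) I have thoughts of killing myself, but I would not carry them out"; C expresses a wish to die by suicide; D says the person would act given the chance.

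The action depends on the option chosen. "If participants choose either C or D, a message including contact information for 2 suicide hotlines will appear"; the study therapist is also notified automatically and phones within 24 hours at most. For the other two options, "If participants endorse A or B, they will simply be allowed to continue with the program".

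The Depressive Symptoms section mentions the same monitoring only as a weekly question. The Treatment-As-Usual Control Condition section explains that the trial was deliberately opened to people reporting suicidal ideation, and expects that they will probably need further mental health services.

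**The concern.** The entry definition joins its two elements with an "or", so a plan alone is enough to count as active ideation and to prompt a referral. The weekly question, which is the only ongoing risk check described, drops the plan element. The same clinical state could therefore lead to a referral on the day of enrollment and to nothing some weeks later.

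What is at stake is the safety of a group that the trial knowingly admits. The program is self-help and the study involves no in-person contact, so study staff have few other occasions to notice a change in risk.

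**Working it through.** No arithmetic applies. The check traces each state to its stated action and looks for any other route that would catch it.

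**Step 1: what each check grades.** The entry check asks about a plan or intent. In the weekly question, A and B separate no thoughts from thoughts without readiness to act, C adds a wish, and D adds readiness to act. None of the four statements refers to a plan.

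**Step 2: trace the states.**

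| State | Stated action at enrollment | Best-fitting weekly answer | Stated action on that answer |
|---|---|---|---|
| Thoughts, no plan, no intent | May take part; weekly question if PHQ-9 item 9 is endorsed | B | None |
| Plan, says would not act | Referral to in-person resources; not enrolled | B | None |
| Wish to die by suicide | No referral stated on a wish alone | C | Hotline message, therapist notification, call within 24 hours |
| Intent | Referral to in-person resources; not enrolled | D | Hotline message, therapist notification, call within 24 hours |

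The second row is the gap. Answer B turns on whether the person would act, so a plan combined with a denial of acting fits it. The first and second rows then give the same answer, and the weekly check cannot tell them apart.

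**Step 3: look for another route.**

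- The Depressive Symptoms section sends an endorsement of PHQ-9 item 9 to the weekly question and to nothing else.
- The diagnostic interviews take place only immediately after the intervention and 16 weeks later, and no suicide-risk action is attached to them.
- The two treatment-condition sections permit outside psychological care but do not arrange it.

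No section states an alert or referral for a participant who answers B.

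**Step 4: does the answer depend on who is enrolled?** The Inclusion and Exclusion Criteria section says "Though the original funded protocol excluded individuals reporting active suicidal ideation", and that "we have since decided to remove these exclusion criteria in order to closely estimate" real-world effectiveness. Participant Safety still keeps such people out of the study. Whichever governs, the weekly question has no plan element, so the trace does not change.

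**The case against.** The strongest reply is that these are two instruments with two purposes. The entry check is a researcher's judgement about enrollment; the weekly question is an automated screen. The protocol promises that the level of risk will be reassessed, not that the entry definition will be applied again. Setting the alert at C and D is an explicit choice, and in one respect it is the wider net: a wish alone triggers a call during the trial, while no referral is stated for a wish alone at entry. This stands in part. It means the two rules are not a formal contradiction. It does not close the gap, because the entry check also triggers a referral, which is a safety action, and nothing equivalent follows a plan formed later.

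A second reply is that the case is narrow. It needs a participant flagged at baseline who forms a plan after entry, disclaims acting on it, and picks B as the best description. This stands.

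A third is that a journal article condenses a fuller protocol. That carries little weight here, because the article prints every option and the action attached to each, including the rule for A and B. Details of what the therapist does on a call may well sit elsewhere, but the trigger is stated outright.

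A reader might infer that anyone with a plan goes undetected. The text does not support that: someone with a plan may choose C or D and be called. A reader might also infer from the Inclusion and Exclusion Criteria section that people with a plan are enrolled from the start. Participant Safety says the opposite, and the document does not settle which governs, so the point should not rest on that reading.

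**Conclusion.** The point holds as a participant-safety gap. A flagged participant who forms a plan after entry but says they would not act can fit answer B and, under the rule as written, receives no hotline message, therapist notification, call or referral, although a plan at the enrollment session leads to a referral.

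The size cannot be given. The document reports no frequency for a plan without declared intent, and no frequency for choosing B rather than C or D when a plan exists. The conclusion rests on two things: that B is a natural answer for someone with a plan who denies they would act, and that no unstated procedure picks up B answers.

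It should not be read as a threat to the trial's results. It has no effect on the outcomes, the analysis or the sample size. It is worth acting on because the remedy is small and the group at risk was admitted on purpose.

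**What to change.** After answer B, branch to one yes/no question on whether the participant has a plan, with wording set by the study therapist. A yes triggers the route that already exists for C and D: hotline message, automatic therapist notification, and a call within 24 hours. A no continues as now.

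If referral to in-person resources is added, apply it equally to C, D and B-with-plan. Participant Safety states no referral for C or D, so adding it only for B-with-plan would give someone who says they would not act more stated steps than someone who says they would.

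The cost is one conditional question in a survey already sent, asked at most once a week and only after B (at most 7 times over the 7-week program), using an alert route already specified. The real downside is therapist time: some extra contacts, which could repeat each week that a plan persists. Their number cannot be predicted from the document, so the study therapist's capacity should be confirmed before the change is made.

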### Primary and Secondary Outcomes

#### Overview

Self-reported psychological outcomes will be assessed immediately postintervention (ie, at the end of the 7th week) and every 2 weeks for 16 weeks. Mood and anxiety disorders will be assessed immediately postintervention as well as 16 weeks postintervention. Finally, health care use will be assessed at postintervention week 16. The control group will follow an identical outcome assessment schedule.

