**Methods:**

We will recruit 170 individuals struggling to become pregnant in Canada or the United States to be randomized to our 7-week self-help program or a treatment-as-usual condition. The primary outcome will be fertility quality of life, while secondary outcomes will include depressive symptoms, anxious symptoms, and relationship quality, assessed before and after the program as well as biweekly for 16 weeks following completion of the program. Self-reported health care use and the presence of diagnosed mood and anxiety disorders, assessed through a structured psychiatric interview, will also be assessed immediately following the intervention and at the 16-week follow-up assessment. Treatment adherence and retention will also be recorded throughout the intervention. Multilevel modeling will compare the intervention arm to the treatment-as-usual condition in terms of all continuous outcomes across the 9 measurement points. Logistic regression will be used to assess the occurrence of mood and anxiety disorders in the 2 treatment arms at the posttreatment assessment as well as at the 16-week follow-up. Sensitivity analyses will examine potential treatment moderators: membership in the LGBTQIA+ (lesbian, gay, bisexual, transgender, queer, intersex, and asexual) communities, baseline fertility quality of life, cultural background, disability status, and pursuit of conception through medical intervention.

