**Results:**

We expect our intervention to be more effective than treatment-as-usual in improving all mental health parameters assessed and decreasing health care use related to both mental and reproductive health. Effects are expected to be larger with decreasing baseline quality of life and equally effective regardless of membership in the LGBTQIA+ communities, cultural background, or disability status.

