## Introduction

### Overview

The Canadian Community Health Survey reveals that 16% of Canadian reproductive-aged couples are currently infertile [1], defined as being unable to achieve pregnancy despite ≥12 months of focused attempts to conceive. Although male- and female-factor infertility are equally prevalent, women bear the brunt of the infertility-related burden as treatments require that women monitor their menstrual cycles, attend near-daily ultrasounds, self-inject gonadotropins, and undergo invasive and painful procedures. Women who travel for fertility treatments face additional psychosocial burdens, including schedule disruptions, time off work, and coordination of care among multiple health care providers. It is therefore not surprising that women carry a disproportionate share of the psychological burden associated with infertility, with infertile women consistently reporting lower self-esteem, more instances of depressed mood and anxiety, and lower life satisfaction than their male partners [2]. Lesbian couples pursuing sperm donation experience similar distress, with the intended pregnant individual being at higher risk for depression and anxiety relative to their partner [3].

Around 30%-40% of women presenting for the evaluation of infertility report clinical symptoms of depressed mood and/or anxiety [4-7]. In addition, research from our team [8] suggests that the COVID-19 pandemic has exacerbated distress amid fertility treatment suspensions and delays. Untreated symptoms of depressed mood and anxiety among women with infertility may, in turn, reduce the likelihood of achieving pregnancy, given that psychological burden is the most commonly cited reason for prematurely discontinuing fertility treatments [9]. In a study of 450 couples who were offered 3 government-funded in vitro fertilization (IVF) cycles, 54% did not complete all 3 cycles despite not achieving pregnancy, with “psychological burden” being the primary reason for discontinuing IVF [10]. It is critical that women with infertility who are distressed receive effective mental health treatment to reduce distress and improve conception rates.

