#### Health Care Use

The questionnaire on health care consumption and productivity losses for patients with a psychiatric disorder will be administered 16 weeks following the intervention, asking participants to report on health care use in the last 4 months. This survey has shown good agreement with hospital- and employer-confirmed data. An additional section has been added to specifically ask about the receipt of fertility treatments.

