If our intervention proves effective, we will aim to make our mobile app publicly available through the Apple Store and Google Play Store. Decreased health care use in the treatment arm relative to the treatment-as-usual arm would provide a strong rationale for seeking government funding to upkeep the Coping with Infertility mobile app, which would allow us to make the program available free of charge. We would provide flyers and posters to fertility clinics across North America, to be posted in clinic waiting rooms and physician offices. We will reach out to relevant professional societies and nonprofit organizations, asking them to include the app as a mental health resource listed on their website. Online forums relevant to infertility will also be contacted and asked to share information related to the app. A YouTube channel will be created to house all of the weekly module videos along with a professionally produced animated explainer video introducing the intervention and describing the results from the trial supporting its efficacy. Final, we will publish our findings in open-access journal articles in respected scientific journals.

In addition to disseminating the Coping with Infertility program as a stand-alone intervention, it may also be worthwhile to pair it with other traditional mental health resources. For example, future research pairing the Coping with Infertility program with infertility support groups, or with individual psychotherapy may help target a broader audience of individuals experiencing infertility-related distress who wish to benefit from peer or therapist support. Translating the content of the program into a workbook format may also appeal to a subset of the target population.

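### Health care use has two different assessment schedules, and lower fertility-treatment use is counted as benefit although it could mean conception or giving up treatment

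*Protocol article*

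**What the plan says.** **Timing.** The Abstract (Methods) pairs self-reported health care use with the diagnostic interview and says that these "will also be assessed immediately following the intervention and at the 16-week follow-up assessment". The Methods, under Primary and Secondary Outcomes, Overview, separate the two. Mood and anxiety disorders keep both time points, and for the other outcome the text reads: "Finally, health care use will be assessed at postintervention week 16". The Health Care Use section also has one administration. The questionnaire "will be administered 16 weeks following the intervention, asking participants to report on health care use in the last 4 months".

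**Content.** The same section extends the questionnaire: "An additional section has been added to specifically ask about the receipt of fertility treatments".

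**Expected direction.** The Abstract (Results) expects the program to do better than treatment-as-usual in "decreasing health care use related to both mental and reproductive health". The Discussion (Significance of the Study) also expects lower use in the treatment arm and then says what would follow: "Decreased health care use in the treatment arm relative to the treatment-as-usual arm would provide a strong rationale for seeking government funding".

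**Rationale.** The Introduction (Overview) says that "psychological burden is the most commonly cited reason for prematurely discontinuing fertility treatments". It cites a study of 450 couples in which 54% did not complete three funded IVF cycles although they had not conceived. It also expects effective treatment of distress to improve conception rates.

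**The concern.** Two matters are at stake.

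First, the two schedules produce different data. One gives a single measurement that largely matches the follow-up period. The other adds a measurement at the end of the program, with no recall window stated for it. A reader of the final report could not tell which was planned.

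Second, fertility-treatment use has no clear good direction in this population. If distress drives people out of treatment, a program that relieves distress may keep them in it, so use would hold or rise. If relief of distress leads to more conceptions, use would fall. A fall could also mean that participants abandoned treatment, which is the harm the Introduction describes. The stated expectation treats every fall as favorable, and the Discussion would take an undivided decrease to a funder.

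**Working it through.** **1. Stated figures.** The article gives no sample size, power or effect size for health care use. Its only such figures, 128 evaluable and 170 recruited, concern FertiQoL and do not depend on this point.

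**2. Schedules side by side.**

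| Place | Time points for health care use | Recall window |
|---|---|---|
| Abstract, Methods | End of program and 16 weeks later | Not stated |
| Primary and Secondary Outcomes, Overview | 16 weeks after the program only | Not stated |
| Health Care Use | 16 weeks after the program only | 4 months |

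The Overview gives the diagnostic interview two time points and health care use one, so it separates what the Abstract joins. Loose wording does not explain the difference.

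**3. Coverage of a single week-16 administration.** Inputs are a 4-month recall (Health Care Use), a 7-week program and a 16-week follow-up (Overview). An average month is taken as 30.4375 days.

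- Recall window: 4 × 30.4375 / 7 = 17.4 weeks.
- Program weeks reached: 17.4 − 16 = 1.4.
- Program weeks not reached: 7 − 1.4 = 5.6.

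**4. Coverage if the questionnaire is also given at the end of the program.** The article states no recall window for this administration. If the 4-month recall were reused (an assumption), 17.4 − 7 = 10.4 of its 17.4 weeks would fall before randomization, taking the program to start at randomization. Most of that report could not be affected by treatment. A recall starting at randomization would cover 7 weeks, and with the follow-up the two administrations would cover 7 + 16 = 23 weeks. The 4-month window at week 16 would then overlap the first by about 1.4 weeks.

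**5. Direction, by component.**

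- *Mental health care.* An expectation of lower use does not conflict with the Introduction.
- *Fertility treatment, higher or sustained use.* This follows if less distress means fewer premature discontinuations.
- *Fertility treatment, lower use.* This follows from more conceptions or from more discontinuation without pregnancy. The two have opposite meanings and look the same in a measure of use alone.

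The documents give no figure from which the balance of these pathways could be computed, so no size is put on it here.

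**The case against.** The strongest reply is that this is a secondary outcome in a condensed article, and that several stronger criticisms a reader might infer do not stand.

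- *The expected direction contradicts the rationale.* The documents do not support this. The Introduction also expects better conception rates, which would lower later fertility-treatment use. The direction is ambiguous, not contradictory.
- *A decrease cannot be shown without a baseline measure.* The Abstract and Discussion compare the program with treatment-as-usual, and a randomized between-arm comparison needs no baseline value.
- *Nothing relevant is recorded earlier.* That holds only for this questionnaire. Fertility-treatment status is the stratification factor (Randomization Scheme), reproductive history and medications are surveyed (Demographic and Medical Information), and both arms report other psychological interventions (Treatment Conditions). None of these settles when the questionnaire is given.
- *Components will cancel in a total, or a rise will count as failure.* No summed score, success rule or one-sided test is stated. Scoring may properly sit in the analysis plan, and the added fertility section already allows the components to be separated.
- *A window matched to follow-up is a fault in itself.* It is a defensible choice if it is the intended one.

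All of these replies stand. Two things remain. The article states two incompatible schedules, which is not an omission that another document would fill. And its own text names lower reproductive care use as a benefit and builds a funding argument on an undivided decrease.

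**Conclusion.** The timing conflict is explicit and needs no inference: two time points in the Abstract, one in both Methods passages. Under the Methods version the questionnaire misses about 5.6 of the 7 program weeks. This assumes average-length months and a program that starts at randomization.

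The expected direction is sound for mental health care and ambiguous for fertility treatment. A lower figure in the treatment arm could not be read as benefit without knowing whether participants stopped because they conceived.

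The point is minor. It concerns one secondary outcome and how it is interpreted, and leaves the primary analysis and the sample size untouched.

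**What to change.** 1. Make the Abstract, the outcomes Overview and the Health Care Use section agree on the assessment times, and state the recall window for each administration.
2. If one time point is intended, correct the Abstract and say that the measure describes essentially the follow-up period.
3. If two are intended, start the week-7 recall at randomization so that it does not reach into the period before it, and say how the overlap of about 1.4 weeks with the week-16 window is handled. The instrument is described here with a 4-month recall, so the shorter window should be acknowledged as a departure.
4. Analyse mental health care use and fertility-treatment use as separate between-arm outcomes. Keep the expected direction for mental health care only.
5. Report fertility-treatment use without a success direction, separating stopping because of pregnancy from stopping without pregnancy.
6. Limit the funding argument in the Discussion accordingly, so that an undivided decrease is not offered as evidence of benefit.

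The cost is mostly wording. Two time points would add one web questionnaire at week 7. Item 5 needs the reason for stopping treatment, or pregnancy status, to be recorded alongside the fertility section if it is not already.
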